### Study visits and assessment

Study duration will be 50 weeks, comprised of a 2-week run-in period, 24 weeks of intervention, and 24 weeks of follow-up. After treatment commences, visits will occur every 4 weeks during the intervention period. During the follow-up period, participants will be asked to visit at 28, 36, and 48 weeks. An overview of specific measurements and time points of data collection can be found in Table 3.

**Table 3 Tab3:** Schedule of enrollment, allocation, visits, and assessments

	Study Period										
	Enrollment	Allocation	Intervention						Follow-up		
Time point (weeks)	−2	0	4	8	12	16	20	24	28	36	48
Eligibility screen	√										
Written informed consent	√										
Medical history	√										
Physical examination		√	√	√	√	√	√	√			
Routine blood and urine		√		√		√		√			
Electrocardiogram		√		√		√		√			
ALT, AST, ALP, GGT, TBIL		√		√		√		√			
24 h urinary protein		√	√	√		√		√	√	√	√
Serum Cr, eGFR		√	√	√		√		√	√	√	√
TC, TG, LDL-C, HDL-C		√	√	√		√		√			
A1C, CRP		√		√		√		√			
Evaluation of TCM syndrome		√	√	√	√	√	√	√	√	√	√
Drug distribution		√	√	√	√	√	√				
Retrieval of unused drugs			√	√	√	√	√	√			
Adverse events			√	√	√	√	√	√	√	√	√

*Abbreviations*: *A1C* hemoglobin A1C, *ALP* alkaline phosphatase, *ALT* alanine transaminase, *AST* aspartate aminotransferase, *eGFR* estimated glomerular filtration rate, *GGT* gamma-glutamyl transpeptidase, *LDL-C* low-density lipoprotein cholesterol, *serum Cr* serum creatinine, *TBIL* total bilirubin, *TC* total cholesterol, *TCM* traditional Chinese medicine, *TG* triglycerides, *HDL-C* high-density lipoprotein cholesterol

√ = Action items

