### Outcome measurements

#### Primary endpoint

The primary endpoint is 24 h UP. The change in 24 h UP from baseline to 24 weeks will be the analysis metric for the difference between the two groups. At baseline and treatment endpoint (24 weeks), the average values of two different samples collected within 1 week will be used to minimize variation between the different urine samples.

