### Sample size estimation

The sample size was estimated based on results from our preliminary trial. These results found that after a 24-week treatment period, the mean reduction in 24 h UP in the placebo group was 0.40 ± 0.91 g; the mean reduction in 24 h UP in the TSF group was −0.31 ± 0.95 g. The least-squares mean of the difference value between the relative changes from baseline (TSF group-placebo group) was −0.54. The proportion of the cases between the TSF group and placebo group will be 1:1. With 80 % power to detect and a two-sided level of significance of 0.05, the sample size was estimated to be 54 in each group. In order to increase the accuracy of the data obtained, this number was increased to 60. Assuming a dropout rate of 20 %, the final sample size was estimated to be 144.

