### Statistical analysis

This trial will use three analysis sets: the intention-to-treat set, which will regard all participants as randomized regardless of whether or not they received the randomized treatment; the per protocol analysis set, which will be restricted to participants who complete the 24-week treatment and/or have the primary endpoint measurement records of at least three time points during the study; and the safety analysis set, which will include randomized participants who have made at least one visit. Multiple imputation analysis will be performed to account for the effect of missing data. Partially missing data will be carried forward with the principle of the last observation carried forward (LOCF). A *P* value less than 0.05 will be considered significant. SAS 9.2 software (SAS Institute, Cary, NC, USA) will be used for analysis.

Continuous variables will be expressed as the mean (SD), and categorical variables, as numbers and percentages. To compare baseline data between the two groups, independent *t* tests (or the Mann–Whitney U test) will be used to analyze continuous data, and chi-square or Fisher exact test will be used for categorical data. Outcome analysis will be performed using *t* test for normally distributed data and rank sum test for non-normal distribution data. Considering that the baseline 24 h UP and/or A1C are essential for the progression of urinary protein, analysis of covariance (ANCOVA) using 24 h UP and/or A1C as covariates will be performed to analyze the 24 h UP reduction at 24 weeks. To investigate the effects of treatment and time course, repeated measures analysis of variance (ANOVA) will be applied to determine changes in the 24 h UP and eGFR at each visit. For safety endpoints, incidences of DILI and BMS will be analyzed by Kruskal-Wallis test, and the incidence of QTc will be evaluated by a chi-square test. For AE evaluation, all AEs will be reported including its grade, time of occurrence, duration, treatment, prognosis, and correlation with the intervention drugs. The chi-square test or Fisher exact test will be used to compare the incidence of AEs between the two groups.

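### 24 h UP is averaged over two collections only at weeks 0 and 24, so a repeated measures ANOVA with one pooled error can misstate visit-level precision, in either direction (minor)

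*Protocol article*

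**What the plan says.** All references are to the protocol article.

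- **Primary endpoint:** "At baseline and treatment endpoint (24 weeks), the average values of two different samples collected within 1 week will be used". The stated reason is to reduce sample-to-sample variation. The metric is fixed in the same section: "The change in 24 h UP from baseline to 24 weeks will be the analysis metric for the difference between the two groups".
- **Study visits and assessment, Table 3:** the row "24 h urinary protein" has eight check marks, read in order as weeks 0, 4, 8, 16, 24, 28, 36 and 48. Two of these visits are averaged. For the other six no averaging is stated.
- **Statistical analysis, time course:** "repeated measures analysis of variance (ANOVA) will be applied to determine changes in the 24 h UP and eGFR at each visit". No error term, covariance structure or sphericity correction is given.
- **Statistical analysis, week 24:** this comparison has its own tests. The sentence beginning "Outcome analysis will be performed using" names a t test or a rank sum test. In addition, "analysis of covariance (ANCOVA) using 24 h UP and/or A1C as covariates will be performed to analyze the 24 h UP reduction at 24 weeks".

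**The concern.** Averaging two collections with independent errors halves the collection-noise variance at that visit. The plan does this at two of eight visits, so the values entering the time-course analysis are not equally precise, even with complete data and even within the on-treatment visits alone.

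In its usual univariate form, repeated measures ANOVA uses one pooled within-patient error and assumes that all between-visit differences have the same variance (sphericity). The sampling scheme does not support that assumption. A degrees-of-freedom correction for non-sphericity repairs the overall time and interaction tests, but it does not give each visit contrast its own variance.

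At stake is how the visit-by-visit arm differences read in this supporting analysis. Week 24 matters most, because that is where the second collection was added to gain precision.

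**Working it through.** The plan states no figure for the repeated measures analysis, so there is none to reproduce. Only the pilot SDs, the effect of 0.54 and the 60 per group are taken from Sample size estimation. (Its 54 per group is not an input here. It does not follow from these SDs and 0.54, which give 47 per group, but that is a separate matter.)

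**Inputs**
- SD of the 24-week change: placebo "the mean reduction in 24 h UP in the placebo group was 0.40 ± 0.91 g"; TSF "the mean reduction in 24 h UP in the TSF group was −0.31 ± 0.95 g". The ± figures are read as SDs. Pooled: √((0.91² + 0.95²)/2) = √0.8653 = 0.93 g. I assume this SD applies to the planned duplicate-average change.
- 60 per arm. Effect 0.54, taken to be in g; the article gives no unit.
- Day-to-day SD of one collection, s: not in the article. Assumed 0.4 to 0.7 g, with independent errors.

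**Step 1. Collection noise is the only difference between visits.** Let the error variance at a visit be t² + m·s², with m = 0.5 at weeks 0 and 24 and m = 1 elsewhere. The term t² is all other within-patient variance and is taken as equal at every visit. The week-24 change then has variance 2t² + s² = 0.93² = 0.8649, so t² = (0.8649 − s²)/2.

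Mean m is (2×0.5 + 6×1)/8 = 0.875 over eight visits, and (2×0.5 + 3×1)/5 = 0.8 over weeks 0 to 24. The pooled error is t² + (mean m)·s². The ratio of pooled to actual SE at week 24 is √(2 × pooled error / 0.8649).

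| s (g) | t² | Pooled error, 8 visits | Ratio | Pooled error, 5 visits | Ratio |
|---|---|---|---|---|---|
| 0.4 | 0.352 | 0.492 | 1.07 | 0.480 | 1.05 |
| 0.7 | 0.187 | 0.616 | 1.19 | 0.579 | 1.16 |

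So the week-24 SE is 5 % to 19 % too large. At the other visits the actual variance of the change is 2t² + 1.5s², and the pooled SE is 1 % to 5 % too large.

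**Step 2. Effect on a week-24 test taken from the pooled ANOVA (eight visits).** The actual SE is 0.93 × √(2/60) = 0.170 g, so 0.54 g is 3.18 SEs. The effective critical value is 1.96 × ratio.
- Correct SE: power Φ(3.18 − 1.96) = 89 %.
- s = 0.4: critical value 2.09, power Φ(1.09) = 86 %, actual two-sided level about 3.6 %.
- s = 0.7: critical value 2.34, power Φ(0.84) = 80 %, actual two-sided level about 1.9 %.

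A simulation of the pooled-error ANOVA (20,000 trials per setting) gave levels of 3.9 % and 2.0 %, and power of 86 % and 80 %.

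**Step 3. True change is not equally variable at every visit.** Let p be the share of the week-24 change variance that is collection noise: 0.16/0.8649 = 0.18 for s = 0.4 and 0.49/0.8649 = 0.57 for s = 0.7. Now pool the variance of the change scores over post-baseline visits. A change to week 24 carries noise s²; a change to any other visit carries 1.5s².

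- *True-change variance rising linearly to week 24, visits to week 24 only.* Mean relative true variance is (4+8+16+24)/(4×24) = 0.542. Mean relative noise is (3×1.5+1)/4 = 1.375. Ratio = √(0.542(1−p) + 1.375p): 0.83 at s = 0.4 and 1.01 at s = 0.7.
- *The same rise, then a plateau, eight visits.* Mean relative true variance is (4+8+16+24×4)/(7×24) = 0.738. Mean relative noise is (6×1.5+1)/7 = 1.429. Ratio: 0.93 to 1.06.
- *The same rise, then a linear decline to zero at week 48, eight visits.* Mean relative true variance is (4+8+16+24+20+12+0)/(7×24) = 0.5. Ratio: 0.82 to 1.01.

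If p is allowed to run from 10 % to 100 %, the last case spans 0.77 to 1.20. The pooled SE can thus be up to 23 % too small.

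**Step 4. Variance estimated separately at each visit.** The ratio is 1.0 in every case.

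**The case against.** A reader might infer that the plan treats all visits as equally precise and that the week-24 error bar is therefore too wide. The article supports neither statement.

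- **Pooling is not stated.** The article names repeated measures ANOVA but gives no error term or covariance structure. A multivariate version, or visit contrasts that each use their own error, goes by the same name and avoids the problem. Such detail is commonly left to an SAP, which is not shown. This stands, so the point has to be conditional on the usual univariate form. It is not a complaint about missing detail: the named method, read in its ordinary sense, does not fit the sampling scheme laid down in the same article.
- **The direction is not fixed.** Too wide requires equal true-change variance at all visits. The article gives an SD for the 24-week change only, and step 3 shows that the sign can reverse. This stands.
- **The noise may not be halved exactly.** The two collections fall within one week, and variation shared across that week does not average out. LOCF could also place a single-collection value at week 24. Both would reduce the contrast in precision. This stands.
- **The primary comparison is untouched.** The t test, rank sum test and ANCOVA use the week-24 change alone, planned as duplicate averages, so the gain from the second collection is kept where the main conclusion is drawn. This stands and limits the weight of the point.
- **The harm is small.** In the too-wide case the error is conservative, and the lowest power in step 2 is 80 %, equal to the design target. That is fair for that case, but the reassurance does not extend to the too-narrow case.

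**Conclusion.** The point holds in a conditional form and is minor. Unequal measurement precision across visits is built into the design: two averaged visits, and six with no averaging stated. With one pooled within-patient error, visit-level precision of 24 h UP in the time-course analysis can be misstated. At week 24 the SE is about 5 % to 19 % too large if collection noise is the only difference between visits, day-to-day errors are independent and their SD is 0.4 to 0.7 g. Over the same SD range it can be as much as 18 % too small (ratio 0.82) if true change spreads out by week 24. Neither the day-to-day SD nor the pattern of true-change variance is in the article, so size and sign are both open. The planned week-24 t test, rank sum test and ANCOVA are not affected.

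**What to change.** In Statistical analysis, replace the repeated measures ANOVA of 24 h UP with a mixed model for repeated measures: arm, visit, arm-by-visit interaction and baseline 24 h UP as fixed effects, with an unstructured within-patient covariance. Report the arm contrast at each visit, with its confidence interval, from that model. Each visit then has its own variance, so the remedy works whichever way the pooled error would have erred.

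The cost is one sentence of analysis text. No extra collections are needed, and the model runs in the SAS version already named. The trial was still recruiting at publication, so the change could be made before unblinding. The downside is 7×8/2 = 28 covariance parameters for seven post-baseline visits, with about 60 patients per arm. A heterogeneous-variance structure should be named in advance as the fallback if the model does not converge.

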#### Secondary endpoints

Secondary endpoints will be as follows:Change in serum creatinine (SCr) and eGFR (2009 CKD-EPI creatinine equation [25]) from baseline to 24 weeksChange in blood lipid profile of total cholesterol (TC), triglyceride (TG), high-density lipoprotein cholesterol (HDL-C), and low-density lipoprotein cholesterol (LDL-C) from baseline to 24 weeksImprovement in TCM symptoms (evaluation by TCM symptom score scale) from baseline to 24 weeksSafety assessment: Results of routine blood and urine tests, electrocardiogram (ECG), alanine aminotransferase (ALT), aspartate aminotransferase (AST), alkaline phosphatase (ALP), gamma-glutamyl transpeptidase (GGT), and serum total bilirubin (TBIL) tests will comprise the comprehensive safety assessment. The safety endpoints will include the incidence and severity of drug-induced liver injury (DILI) and bone marrow suppression (BMS), as well as the incidence of QTc prolongation, as measured by ECG. DILI is defined by criteria established by the International Serious Adverse Events Consortium [26]. The causality relationship between DILI and the intervention drug will be assessed with the Roussel Uclaf Causality Assessment Method (RUCAM) [27]. Severity is scored on a range from 1 (mild) to 5 (fatal) [28]. The diagnosis and severity of bone marrow suppression will be assessed by criteria established by the World Health Organization Collaborating Centre for International Drug Monitoring [29]: grade I: white blood cell (3.0–3.9) × 109/l, hemoglobin 95–100 g/l, platelet (75–99) × 109/l; grade II: white blood cell (2.0–2.9) × 109/l, hemoglobin 80–94 g/l, platelet (50–74) × 109/l; grade III: white blood cell (1.0–1.9) × 109/l, hemoglobin 65–79 g/l, platelet (25–49) × 109/l; grade IV: white blood cell (0–1.0) × 109/l, hemoglobin < 65 g/l, platelet < 25 × 109/l. QTc longer than 0.44 second is regarded as prolongation.

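### Cheap improvement: the only between-arm QTc comparison named is a chi-square on values above 0.44 s; a baseline-adjusted analysis of the scheduled ECGs could be added beside it

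*Protocol article*

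**What the plan says.** Under Secondary endpoints, the safety endpoints are drug-induced liver injury, bone marrow suppression, "as well as the incidence of QTc prolongation, as measured by ECG". The definition is a single threshold: "QTc longer than 0.44 second is regarded as prolongation".

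Under Statistical analysis, the sentence on safety endpoints assigns QTc its own test: "the incidence of QTc will be evaluated by a chi-square test". No other between-arm QTc comparison is named. The same section gives 24 h UP a covariate-adjusted analysis and applies repeated measures ANOVA to 24 h UP and eGFR. It also has a general rule (t test or rank sum test for outcomes, mean and SD for continuous variables) that does not mention QTc.

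Table 3, under Study visits and assessment, has a row "Electrocardiogram" with ticks at weeks 0, 8, 16 and 24.

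**The concern.** Each ECG gives a number in milliseconds. Once that number is cut at 440 ms, a patient who goes from 400 to 439 ms counts as unchanged, and a patient at 441 ms counts the same as one at 520 ms. The week-0 value, which could remove much of the between-patient variation, plays no stated part in the comparison. The three on-treatment values enter only as above or below the cut.

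The stated purpose of the trial is to establish safety as well as efficacy, and QTc is one of three named safety endpoints. If TSF shifted QTc moderately in most patients, a chi-square on the cut could fail to show it although the scheduled ECGs could have done so.

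**Working it through.** **Plan's own figure.** There is none to reproduce. The article states no power, mean, SD, rate or expected shift for QTc. The trial is sized on 24 h UP.

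**Inputs from the article.** The cut is 440 ms. Allocation is 1:1 and 144 are to be randomised, so 144 / 2 = 72 per arm; 60 per arm are expected after dropout. Significance is at 0.05. Two-sidedness is stated for the sample size ("a two-sided level of significance of 0.05") and is assumed here for QTc.

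**Assumed, because the article does not give them.** Control mean μ = 410, 420 or 430 ms; between-patient SD σ = 20, 25 or 30 ms; equal correlation r = 0.5 or 0.7 between any two visits; normal values; every TSF patient shifted by the same d ms after week 0. The article does not say which visits count for incidence. The main comparison takes a patient as prolonged if any of the week 8, 16 or 24 values exceeds 440 ms.

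**Formulas.**

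1. Share prolonged at any on-treatment visit: p = 1 − ∫ φ(u) · Φ((440 − μ − σ√r·u) / (σ√(1−r)))³ du, with μ + d in place of μ for TSF.
2. Chi-square power: Φ([|p1 − p0| − 1.96·√(2p̄(1−p̄)/n)] / √([p0(1−p0) + p1(1−p1)]/n)).
3. Power of a comparison of means: Φ(d / (s·√(2/n)) − 1.96), where s = σ√(1−r²) for ANCOVA at week 24 and s = σ√((1+2r)/3 − r²) for ANCOVA on the mean of the three visits.

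**Central case** (μ = 420, σ = 25, r = 0.5, d = 10, n = 72):

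- Any-visit chi-square: p0 = 0.407, p1 = 0.586, p̄ = 0.4965. The null SE is √(2 × 0.4965 × 0.5035 / 72) = 0.0833 and the alternative SE is 0.0820. Power = Φ((0.1794 − 1.96 × 0.0833) / 0.0820) = Φ(0.20) = 58%.
- ANCOVA, week 24: s = 25 × √0.75 = 21.65; SE = 21.65 × √(2/72) = 3.61. Power = Φ(10/3.61 − 1.96) = Φ(0.81) = 79%.
- ANCOVA, three-visit mean: s = 25 × √(2/3 − 0.25) = 16.14; SE = 2.69. Power = Φ(10/2.69 − 1.96) = Φ(1.76) = 96%.

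Simulation of the same case gave 58 to 60%, 76 to 80% and about 95%.

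**Grid of 18 cells** (3 means × 3 SDs × 2 correlations), 72 per arm, formulas above. Gaps are in percentage points of power relative to the any-visit chi-square.

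| Shift (ms) | Gap to week-24 ANCOVA | Cells with gap ≥ 20 | Gap to three-visit ANCOVA | Cells with gap ≥ 20 |
|---|---|---|---|---|
| 5 | 6.6 to 37.2 | 7 of 18 | 19.6 to 58.5 | 17 of 18 |
| 8 | 15.4 to 50.8 | 14 of 18 | 39.5 to 60.4 | 18 of 18 |
| 10 | 17.2 to 44.0 | 16 of 18 | 23.4 to 57.1 | 18 of 18 |
| 15 | 1.7 to 29.0 | 4 of 18 | 1.8 to 30.2 | 6 of 18 |
| 20 | 0.0 to 9.8 | 0 of 18 | 0.0 to 9.8 | 0 of 18 |

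At 10 ms, simulation gave minimum gaps of 14 points (week-24 ANCOVA) and 21 points (three-visit ANCOVA), slightly below the normal approximation. With 60 per arm the central case is 50% against 72% and 92%.

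**A non-uniform effect.** If 15% of TSF patients rise by 60 ms and the rest do not change, with mean 400 and SD 15 ms, simulation gives about 95% for any-visit chi-square, against 77 to 79% (week-24 ANCOVA) and 87 to 88% (three-visit ANCOVA). At means of 410 to 420 ms the three-visit ANCOVA was again ahead.

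**The case against.** The strongest objection is that nothing is misstated. The endpoint is an incidence, and chi-square is a suitable test of an incidence. A prolongation endpoint asks how many patients cross a threshold; a comparison of means asks a different question. Faulting the chi-square for low power against a uniform shift judges it on a question it was not set. If a few patients respond strongly, it can be the better test. This objection stands, and it rules out replacing the chi-square.

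A second objection is that every QTc input is assumed, that the article gives no reason to expect a QTc effect of TSF, and that it claims no power for any safety endpoint. This also stands. The figures show the direction and plausible size of the loss, not its value in this trial.

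Third, a reader might infer that QTc will never be analysed as a number. The article does not support that. Its general rule on t and rank sum tests could be read to cover QTc, and a fuller analysis plan, which is not shown, may contain ECG change tables. What can be said is that the chi-square is the only QTc comparison named, and that the general rule, even if it applied, would use neither the baseline nor the repeated values.

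Fourth, a reader might infer that a non-significant chi-square will be reported as absence of a QTc effect. Nothing in the article says so.

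**Conclusion.** The point holds as a worthwhile addition to a secondary safety analysis. The named comparison leaves the size of change, the baseline value and the repeated measurements unused. For a uniform mean shift of about 8 to 10 ms, with control mean 410 to 430 ms, SD 20 to 30 ms, correlation 0.5 to 0.7 and 72 per arm, the any-visit chi-square commonly has 20 or more points less power than a baseline-adjusted analysis of all on-treatment visits.

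It would be tempting to call 20 points a guaranteed minimum loss. The figures do not support that: the gap falls below 20 in some cells against week-24 ANCOVA, in most cells at 15 ms and in all cells at 20 ms, where both tests approach full power. The ranking can also reverse when only a few patients have large increases. Nor is the chi-square the wrong test for the endpoint as defined.

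**What to change.** In Statistical analysis, keep the chi-square on the incidence of QTc prolongation and add one sentence. It should say that QTc will also be compared between groups as a continuous variable, by ANCOVA on the mean of weeks 8, 16 and 24 or by a mixed model for repeated measures on those visits, adjusted for week-0 QTc. The result should be reported as the TSF-minus-placebo difference in ms with its 95% CI. The confidence interval shows which mean effects the data can exclude, which a P value on the cut does not.

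The cost is one sentence and one more safety model, with no new ECGs, visits or patients. The main downside is that the numeric QTc must be in the database, not only a normal/prolonged flag. With 123 patients already recruited, this may mean retrieving values from existing ECG records; the article does not say how QTc is captured. Allocation is still blinded to the investigators and statistician, so the addition can be specified before unblinding.
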